**Methods:**

We proposed a mixed method study among MSM in Ghana. First, we will develop the intervention protocol using the Convergence Framework, which combines three interventions that were previously implemented separately in Ghana for reducing stigma at the HCF-level, increasing HIV testing at the peer group-level, and increasing peer social support at the individual-level. Then, we will conduct a cluster randomized controlled trial with four pairs of HCFs matched on staff size. HCFs within each pair are randomized to the HCF-level stigma-reduction intervention or control arm. MSM (n = 216) will be randomized to receive the group-level and individual-level interventions or standard of care control arm. MSM will be assigned to receive HIV testing at one of the HCFs that match their study assignment (intervention or control facility). The frequency of HIV testing between MSM in the study arms at 3 and 6 months will be compared, and the predictors of HIV testing uptake at the HCF, peer group and individual-levels will be assessed using multi-level regression models.

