### Sample size

Sample size calculation for MSM participants is based on testing the primary study hypothesis that multi-level intervention will increase the HIV testing rate. Our previous study showed that the 6-month HIV testing rate among MSM was 40%. We hypothesize that this rate will increase to 70% after six months of multi-level intervention. This estimate is based on the evidence from the 3MV trial which showed 81% greater odds of HIV testing in intervention compared to the control group at 6-months and is conservative in comparison to UNAIDS “90-90-90” goals. To determine whether our estimated rate of 70% following interventions is different than the comparison rate of 40% with 80% power and Type I error probability 0.05, while assuming a 10% intra-cluster correlation coefficient, we need 86 MSM participants in each arm, or 172 in two arms by the end of 6-month follow-up. Given a cohort retention rate of 80% (based on retention in previous studies with MSM in Ghana), a total of 216 MSM will be recruited. To evaluate the impact of intervention training on intersectional stigma among staff, we will test whether the training intervention will increase the willingness of HCF staff to provide services to MSM. The historical data shows that the willingness rate is 75%. We expect that the intervention will increase the willingness rate up to at least 90% in the intervention clinic staff, while there is no change in the control group, and we will need 97 staff in each arm, or 194 in total, to achieve 80% power with a 5% Type I error rate.

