### Statistical analysis plan

The intervention outcomes will be assessed using a rigorous intention-to-treat approach where participants are included in the analysis as assigned initially, regardless of whether they receive the multi-level intervention or usual care. First, we will compare baseline data to see if randomization made the groups equivalent. If we determine non-equivalence, then the non-equivalent variables will be accounted for in the final analyses using a difference in differences analytic technique where randomization is used to minimize any perception of bias in the selection of sites by investigators. We will determine the proportions of HIV testing at 3- and 6-month follow-up assessments among MSM with 95% confidence intervals (CI). To test the primary study hypothesis that multi-level intervention will increase the uptake of HIV testing within six months of randomization, we will use an uncorrected chi-square statistic.

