Additionally, multivariable logistic regression will be used to compute the adjusted odds ratio and 95% CI for the binary outcome–HIV testing. The successful uptake of HIV testing can be dependent on the environment in the HCF so that HIV testing among MSM participants at the same HCF may be corrected or “clustered.” To account for the potential post-randomization clustering effect in this individually randomized clinical trial, a generalized linear mixed-effects model with a logit link function will be fitted, and this model includes both HCF cluster-level and MSM individual-level factors. Structural equation modeling will be performed to evaluate the association between the multilevel intervention and uptake of HIV testing while simultaneously assessing the mediation role of intersectional stigma. We will also perform the same analyses for HIV testing within three months of randomization, although the analyses may be underpowered. The likelihood of intervention contamination across the study groups could not be excluded, because some participants may not receive the respective interventions to which they are randomized, e.g., some members of the control group may seek health care at the intervention HCFs during this trial. Therefore, we will also perform per-protocol analysis, which includes only those participants who strictly adhere to the protocol and report the results along with the results of the intention-to-treat analyses. To estimate the effect size of the HP+ intervention for staff, we will compare the rates of willingness to provide healthcare to MSM between the staff in intervention and control HCFs. Chi-square test and t-test will be used for the binary (willingness) and continuous (stigma score) outcomes, respectively. Multivariate logistic or linear regression models will be fitted while adjusting for confounding factors such as sex and job title of the staff.

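### The primary chi-square test ignores facility clustering that the plan itself assumes, so it does not hold its 5% error rate; the planned clustered model should be primary

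*Protocol article*

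**What the plan says.** Four parts of the protocol article bear on this.

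- **Primary test.** The Statistical analysis plan section states, for the hypothesis that the intervention raises testing uptake within six months of randomisation: "we will use an uncorrected chi-square statistic".
- **Sample size.** The Sample size section compares 40% with 70% "with 80% power and Type I error probability 0.05" and continues: "while assuming a 10% intra-cluster correlation coefficient, we need 86 MSM participants in each arm". It names neither the cluster unit nor the cluster size.
- **Allocation.** The Abstract says "HCFs within each pair are randomized to the HCF-level stigma-reduction intervention or control arm". There are eight facilities, hence four per arm. Step 8 (Test) sends intervention men to one of the intervention facilities and control men to any of the control facilities.
- **Clustered model.** After the primary test, the Statistical analysis plan section adds a logit mixed-effects model with facility-level and individual-level factors. Its reason: "To account for the potential post-randomization clustering effect in this individually randomized clinical trial". The title calls the trial cluster randomised.

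**The concern.** By assignment each facility belongs to one arm only. If facilities differ in how readily men get tested there, those differences do not cancel between arms. They become part of the treatment contrast and must enter its standard error. An individual-level chi-square leaves them out. Randomising the men individually does not cure this, because the arm comparison is at the same time a comparison of four facilities with four others.

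The plan accepts the premise twice: it sizes the trial with a positive ICC, and it says that testing can depend on the facility. It then gives the deciding role to the one analysis that assumes no such dependence. A chance difference between two sets of four facilities could be declared an intervention effect well above the stated 5% rate. If the chi-square and the mixed model disagreed, the plan as written would let the chi-square decide.

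**Working it through.** **Inputs.** From Sample size: 40% vs 70%, alpha 0.05 (taken as two-sided), ICC 0.10, 86 completers per arm, 80% retention. From the Abstract and Step 8: eight facilities, four per arm. Derived, not stated: 86/4 = 21.5 completers per facility, assuming equal sizes.

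**1. The plan's own figure.**
- Without clustering, n = [1.96·√(2·0.55·0.45) + 0.8416·√(0.24 + 0.21)]² / 0.30² = 42 per arm.
- The stated 86 implies a design effect (DE) of 86/42 = 2.05. From DE = 1 + (m − 1)·0.10, m is about 11.5. That would need 86/11.5, or about 7.5 clusters per arm; the plan has four.
- With m = 21.5, DE = 1 + 20.5 × 0.10 = 3.05, and 42 × 3.05 = 128 per arm. So 86 does not follow from four facilities per arm.
- The retention step does reproduce: 86/0.8 = 107.5, rounded to 108 per arm, or 216.

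**2. True size of the unadjusted test.** Type I error = 2·[1 − Φ(1.96/√DE)]. With DE = 3.05, 1.96/1.746 = 1.122, giving 26.2%. Simulation (400,000 replicates, four clusters of 21-22 per arm, rate 0.40) gives 27.2%, with beta-binomial and logit-normal facility effects agreeing.

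**3. Sensitivity to what the plan leaves open.** For matching, with f the share of between-facility variance removed, DE = 0.90 + 21.5 × 0.10 × (1 − f).

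| Reading | DE | Type I error |
|---|---|---|
| ICC 0.10, m = 21.5, no matching gain | 3.05 | 26% (simulated 27%) |
| ICC 0.10, m = 11.5 (implied by n = 86) | 2.05 | 17% |
| ICC 0.10, m = 21.5, matching removes half | 1.975 | 16% |
| ICC 0.10, m = 21.5, matching removes three quarters | 1.44 | 10% |
| ICC 0.10, m = 27 (all recruited men) | 3.60 | 30% |
| ICC 0.10, unequal sizes 40/22/14/10 | – | 32% (simulated) |
| ICC 0.05, m = 21.5 | 2.025 | 17% |
| ICC 0.02, m = 21.5 | 1.41 | 10% |

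Matching that removed all between-facility variance would give DE 0.90 and 3.9%.

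**4. Power of a valid test with 172 completers.** At DE = 3.05 the standard error is √[3.05 × (0.24 + 0.21)/86] = 0.126, so the standardised effect is 0.30/0.126 = 2.37.
- Normal approximation: 66%, or 63% with the pooled null variance.
- Noncentral t, no matching gain: 51% on 6 df (eight facilities, two arms), 48% on 5 df (city also fitted), 38% on 3 df (four pairs).
- With four facilities per arm and ICC 0.10, the effective sample size cannot exceed 4/0.10 = 40 per arm, below the 42 needed. More men at the same facilities cannot restore 80% power without a gain from matching.

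**The case against.** The strongest reply has four parts.

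**The 26-27% rests on choices the plan does not make.** A reader might take it as the direct consequence of the stated ICC. It is not: cluster unit and size are unstated, the sample size itself implies smaller clusters, and facilities are matched within city. This stands. The figure needs its assumptions beside it, with the range.

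**Facility membership is looser than four closed clusters per arm.** Control men may use any control facility, tests are also captured by self-report, and the plan expects some crossover. This stands as a reason for caution about the size. It does not make the men independent, and the plan does not claim that it does.

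**A clustered analysis is already planned.** True, so a reader should not infer that the plan has no valid analysis, or that the word uncorrected shows a decision to refuse cluster adjustment; it most likely refers to the continuity correction. The fault is in which analysis is primary.

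**The trial is preliminary.** Study rationale and aims describes feasibility and an effect size for a later trial. A reader might infer that the Aim 2 estimate will have a falsely narrow interval. The documents do not support that: nothing says the estimate comes from the chi-square, and the adjusted odds ratio and its interval come from regression. Still, the plan sets a powered primary hypothesis at 5% error, and the test it names does not deliver that.

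**Conclusion.** The primary test as written is not valid at its stated level under the plan's own assumption of clustering. At ICC 0.10 the two-sided type I error is about 26-27%, provided the facility is the unit of the ICC, completers number 21.5 per facility in equal clusters, and matching brings no gain. It is roughly 16-32% under the other readings of cluster size and balance, and with matching that removes up to half of the between-facility variance. At ICC 0.05 it is about 17%, and at ICC 0.02 about 10%. Only an ICC near zero, or matching that removes nearly all between-facility variance, brings it close to 5%; the plan assumes neither. The direction is therefore firm, and the exact size is conditional. This should be corrected before outcome data are analysed.

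**What to change.** - Make the mixed-effects logistic model already described the primary test, with a facility random intercept, small-sample degrees of freedom suited to eight facilities, and city or matched pair reflected in the model. A cluster-level test on the eight facility proportions is an acceptable alternative.
- Analyse each man under a facility assigned and recorded at randomisation in both arms. Step 8 does not describe such an assignment for controls, although Confidentiality and security of data refers to an assigned facility.
- Keep the chi-square as description only.
- State that the Aim 2 effect size, confidence interval and ICC come from the clustered model.
- Give the cluster unit and size behind the 10% ICC. Reconcile the cluster-randomised and individually randomised labels, and the two matching variables (staff size in the Abstract, number of HIV tests in Step 8).

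**Cost.** Changing the test is a matter of wording, but the consequences are larger. Facility assignment of controls must be recorded. At DE = 3.05 the standard error, and so a normal-based interval, is √3.05 = 1.75 times as wide as an unadjusted one; t-based limits are wider still. The stated 80% power must be restated as about 63-66% by normal approximation and about 51%, 48% or 38% on 6, 5 or 3 degrees of freedom, under the assumptions above. A real gain from matching would improve these figures.

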### Eligibility

#### HCF staff

For the intervention, HCF staff are eligible to participate in the study if they are employed at one of the eight facilities identified for this study and identified with a potential to encounter MSM clients. HCF staff will be excluded if they anticipate leaving work at the HCF during the study period. For the FGDs, HCF staff are eligible to participate in the FGDs if they are employed at a study participating facility. HCF staff who have been previously trained in the HCF HIV stigma-reduction intervention that is being adapted for this study and have previously delivered it in a Ghanaian HCF are eligible for in-depth interviews.

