#### Step 8 (Test)

We will conduct an RCT of the multi-level intervention with a 6-month wait-list control. In each city, we will create two pairs from the 4 HCF sites matched by the number of HIV tests performed in the calendar year 2020. We will randomly assign clinics (enveloped odd/even) within each pair to either receive the HP+ or the wait-list control. MSM will be randomly assigned to receive either Nyansapo and HIVE^3^ or wait-list control. MSM in the intervention group will be asked to follow-up for HIV testing and services at one of the HCFs assigned to the HP+ intervention and the MSM in the wait-list control group will be asked to follow-up at any of the HCFs in wait-list control. Nurses from the intervention HCFs will participate as guest facilitators in one of the Nyansapo sessions and will use that opportunity to reach out to MSM to visit their facility for testing. Our primary hypothesis is that the multi-level intervention will increase uptake of HIV testing among MSM participants. We will use research data collectors to measure frequency of HIV testing among MSM at 3- and 6-months post-intervention using a combination of self-report survey and verification by study nurses (for men who get tested for HIV at participating HCFs.) Our secondary hypothesis is that the multi-level intervention will reduce intersectional stigma that HCF staff convey and that MSM experience in HCFs. We will use research data collectors to administer a survey measuring intersectional stigma 1) in the HCFs at baseline, 3-months post and 6-months post intervention and 2) among MSM at baseline, 3- and 6-months post intervention.

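### The mixed model meant to handle facility clustering compares four facilities with four and takes facility-level covariates; with ordinary large-sample inference its 5% test would run at about 9–18% at the plan's ICC of 0.10

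*Protocol article*

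**What the plan says.** The Abstract (Methods) states that "we will conduct a cluster randomized controlled trial with four pairs of HCFs matched on staff size". Step 8 (Test) forms two pairs in each city and continues: "We will randomly assign clinics (enveloped odd/even) within each pair to either receive the HP+ or the wait-list control". The eligibility text confirms eight sites; staff must be "employed at one of the eight facilities identified for this study". The Abstract and Step 8 both direct men to facilities of their own arm.

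Sample size assumes 40% testing in the comparison arm and an ICC of 10%, and plans 86 evaluable men per arm (172 in all) "with 80% power and Type I error probability 0.05".

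The Statistical analysis plan tests the primary hypothesis with an uncorrected chi-square. It then adds further models, among them a logit mixed model for clustering: "a generalized linear mixed-effects model with a logit link function will be fitted, and this model includes both HCF cluster-level and MSM individual-level factors". The Abstract likewise plans to assess HCF-level predictors in multi-level models. The number of HCF-level factors, the reference distribution and the degrees of freedom are not given. The same section calls the trial individually randomised and treats the clustering as something that arises after randomisation.

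**The concern.** If each facility serves one arm, the arm effect is a between-facility comparison, and its precision depends on how well the between-HCF variance is estimated. Eight facilities estimate it poorly. A logit mixed model read with a normal or chi-square reference treats that variance as known. Each HCF-level factor makes this worse, because it fits part of the little between-facility variation from which the variance is estimated.

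Aim 2 is to estimate an effect size for a definitive trial, so the interval from this model is a main product of the study. An interval that is too narrow would make that effect look more certain than it is. This model is also the natural replacement for the chi-square if the primary test is corrected for clustering, and it would then bring its own inflated error rate with it.

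**Working it through.** **Inputs.** Eight HCFs, four per arm (Abstract; Step 8). Null testing rate 40%, ICC 0.10, 172 evaluable or 216 recruited men (Sample size). These give 172/8 = 21.5 or 216/8 = 27 men per HCF. Assumptions not in the article: two-sided 5%, fixed HCF membership, and ICC on the latent logit scale unless noted.

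**The plan's own figure.** The article states no error rate for the mixed model, so there is none to reproduce. Its 86 per arm does not follow from four HCFs per arm. The design effect is 1 + (21.5 − 1) × 0.10 = 3.05, and 39.24 to 42 per arm × 3.05 gives about 120 to 129. That is a separate matter; 172 is used here as stated.

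**Degrees of freedom.** 8 HCFs − 2 (intercept and arm) − k HCF-level covariates:

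| k | df | t, 97.5% | Width relative to 1.96 |
|---|---|---|---|
| 0 | 6 | 2.447 | 1.25 |
| 1 | 5 | 2.571 | 1.31 |
| 2 | 4 | 2.776 | 1.42 |
| 3 | 3 | 3.182 | 1.62 |

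Three pair indicators count as k = 3.

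**Simulated type I error.** 3,000 null trials per setting; random-intercept logit model fitted by maximum likelihood with 31-point quadrature; ICC 0.10, N = 172, equal HCF sizes:

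| k | Wald z | Likelihood ratio | t on 8 − 2 − k df |
|---|---|---|---|
| 0 | 10.9% | 8.7% | 5.0% |
| 1 | 12.8% | 11.0% | 5.6% |
| 2 | 15.8% | 13.9% | 4.7% |
| 3 | 18.1% | 17.0% | 2.7% |

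The Monte Carlo standard error is at most about √(0.18 × 0.82/3000) = 0.7 percentage points. Near the null, a nominal 95% Wald interval would cover 100 − 18.1 to 100 − 10.9, or about 82–89%.

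**Sensitivity, Wald z:**
- Unequal HCF sizes, k = 0 and 2: 13.3% and 17.8% (t: 6.8% and 5.7%).
- N = 216, k = 0 and 2: 11.7% and 17.2% (t: 5.9% and 6.1%).
- ICC 0.05: 8.8–13.8% (t: 1.2–5.0%).
- ICC 0.01: 5.3–7.4%. With equal sizes, N = 172 and k = 1 to 3, t gives 0.3–1.5%.
- Latent ICC 0.149 (about 0.11 on the proportion scale): 12.0–21.3% (t: 4.5–8.2%).
- ICC 0.10 with matched pairs sharing half of the HCF variance: 6.4% with no covariates, 11.0% with two, 13.9% with pair fixed effects (t: 2.1%, 2.4%, 1.8%).
- Beta-binomial data at ICC 0.10 (1,500 runs), k = 0, 1, 2: 11.6%, 14.9%, 17.7%.

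**The case against.** The strongest reply is that the article never names a z or chi-square reference. Degrees of freedom and covariate lists are ordinary content of a full analysis plan, which is not shown. That stands. A reader might infer that the planned test runs at 10–18%, or that the sponsor has left out a small-sample correction. The text supports neither, and the figures hold only if default large-sample inference is used. What the article does fix is the model itself: HCF-level factors fitted on eight HCFs, in a section that presents the trial as individually randomised although Step 8 randomises clinics.

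Second, the mixed model is additional, and no decision rule hangs on it. That also stands. A reader might infer that the primary conclusion rests on this model, but it rests on the chi-square, which ran at about 21–26% in the same simulations at ICC 0.10. What remains is the interval for Aim 2.

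Third, the size depends on the ICC and on the matching. Informative pairs could bring the error with no covariates down to about 6%. The article gives no evidence of how informative the matching is, and it describes the matching variable as staff size in the Abstract but as 2020 HIV test volume in Step 8.

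Fourth, nesting holds by assignment only. Step 8 lets control men use any control facility, and the analysis section expects some to use intervention facilities. The simulations assume fixed membership.

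Finally, the 10% ICC in the sample size is also an allowance for clustering. The mixed model is the only allowance at the analysis stage.

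**Conclusion.** The concern holds in conditional form. The only analysis said to account for HCF clustering makes a four-against-four comparison with 6 HCF-level degrees of freedom before covariates, and it plans to spend some of those on HCF-level factors. With z or likelihood-ratio inference at the plan's ICC of 0.10 and 0–3 HCF-level covariates, type I error would be about 9–18%, and intervals would be correspondingly too narrow. Across the ICC values and matching assumptions examined, Wald z error runs from about 5% to 21%. The result rests on a large-sample reference that the article does not state, on fixed HCF membership and, for the headline range, on matching that explains little of the variance. It supplements the problem with the chi-square primary test and does not replace it.

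**What to change.** Amend the mixed-model paragraph to say three things:

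1. The arm effect and its interval use a t distribution with 8 − 2 − k degrees of freedom, where k is the number of HCF-level covariates (3 if pair effects are fitted and nothing else is added at HCF level).
2. HCF-level covariates are kept to a minimum, at most one, named in advance. Individual-level covariates stay as planned.
3. An HCF-level summary analysis is reported as a check: a t-test on HCF proportions with 6 degrees of freedom, or 3 if it respects the pairs.

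A permutation test within pairs would not do as the 5% test. Four pairs give 2⁴ = 16 allocations, so the smallest two-sided p-value is 2/16 = 0.125.

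The change is to wording only. The interval widens by about 25% with no HCF-level covariate (2.447/1.96) and by about 31% with one (2.571/1.96). The t reference is also conservative when the between-HCF variance is small or largely shared within pairs, as the low-ICC and shared-pair results show. Limiting the model to one covariate also means that the Abstract's aim of assessing HCF-level predictors has to be treated as descriptive.

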#### Nyansapo intervention (interpersonal/peer-group level)

Nyansapo is a Ghanaian adaptation *of Many Men Many Voices* [43, 48], a group-level behavioral intervention with demonstrated efficacy in increasing odds of HIV testing and reducing in Black MSM in the United States. *Many Men Many Voices* is designated as a best-evidence intervention by the Centers for Disease Control and Prevention (CDC) and is included in the CDC’s compendium of effective HIV prevention interventions [44]. Nyansapo previously demonstrated feasibility and acceptability during pilot program implementation in a community-based organization in Ghana [49]. MSM who are assigned to the intervention condition will be given dates for the weekend intervention retreats they would attend at temporarily rented facilities. Prior to attending Nyansapo, participants will attend an orientation meeting at the offices of local partner organizations to obtain information about the logistics and format of the retreat and to establish ground rules for appropriate behavior. Once participants arrive at the retreat, the Nyansapo intervention will be delivered in six consecutive 2- to 3- hour sessions. The Nyansapo intervention manual will be further refined to focus on intersectional stigma. Individuals assigned to the comparison condition will be offered the chance to participate in Nyansapo after the RCT is completed.

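### Only intervention men are treated in retreat groups, but neither the primary chi-square nor the described mixed model allows for correlation within retreats

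*Protocol article*

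**What the plan says.** In the protocol article, the Nyansapo section says that "MSM who are assigned to the intervention condition will be given dates for the weekend intervention retreats". Men in the comparison arm are offered Nyansapo only once the trial is over, and Table 1 lists its modality as group sessions. During follow-up, retreat groups therefore exist in one arm only.

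The Statistical analysis plan section tests the primary hypothesis with an uncorrected chi-square. It then adds a logistic mixed model to handle clustering that arises after randomization. The only source of clustering it names is sharing an HCF, and it says that "this model includes both HCF cluster-level and MSM individual-level factors".

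The abstract (Methods) says that "the predictors of HIV testing uptake at the HCF, peer group and individual-levels will be assessed using multi-level regression models". The two places therefore differ on whether a peer-group level is modelled.

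The Sample size section applies one ICC: "while assuming a 10% intra-cluster correlation coefficient, we need 86 MSM participants in each arm, or 172 in two arms". It names neither the cluster unit nor the cluster size.

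**The concern.** Men at one retreat share facilitators, sessions and group discussion. Step 8 (Test) adds a direct route to the primary outcome: nurses from intervention HCFs join a Nyansapo session and invite the men to test at their facility. Correlated testing within retreats is therefore plausible, and control men have no counterpart to it.

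The chi-square treats intervention men as independent. The mixed model, as described, picks up retreat correlation only to the extent that retreats coincide with HCFs. If they do not, the p-value is too small and the confidence interval too narrow. This matters for Aim 2, which is to supply an effect size for a definitive trial. That trial would also need a retreat ICC, and this plan does not produce one.

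**Working it through.** **The plan's own figure.** Inputs from Sample size: 40% against 70%, 80% power, alpha 0.05 (two-sided taken), ICC 0.10.
- Without clustering (pooled variance): n = (1.96·√(2·0.55·0.45) + 0.842·√(0.24 + 0.21))² / 0.30² = 42 per arm.
- With the HCF as cluster (8 HCFs, 4 per arm): 86/4 = 21.5 men each, design effect 1 + 20.5·0.10 = 3.05, and 42·3.05 = 128 per arm, not 86.
- 86/42 = 2.05 needs a cluster of 1 + 1.05/0.10 ≈ 11.5 men, a size the article does not state.
- The dropout step agrees: 86/0.8 = 107.5, so 108 per arm and 216 in total.

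The 86 therefore does not show which clustering was allowed for.

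**Effect of retreats on the chi-square.** Assumed, because the article gives neither: m = 8 to 15 analysed men per retreat and retreat ICC ρ = 0.02 to 0.10. HCF clustering is left aside here.
- Design effect in the intervention arm: DE = 1 + (m − 1)ρ. In the control arm it is 1.
- Under no arm difference, true SE / naive SE: f = √((DE + 1)/2).
- Shortfall of the naive SE: 1 − 1/f. Type I error: 2·(1 − Φ(1.96/f)).

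| m | ρ | DE | f | SE too small by | Type I error |
|---|---|---|---|---|---|
| 8 | 0.02 | 1.14 | 1.034 | 3.3% | 5.8% |
| 8 | 0.10 | 1.70 | 1.162 | 13.9% | 9.2% |
| 11 | 0.05 | 1.50 | 1.118 | 10.6% | 8.0% |
| 11 | 0.10 | 2.00 | 1.225 | 18.4% | 11.0% |
| 15 | 0.02 | 1.28 | 1.068 | 6.3% | 6.6% |
| 15 | 0.10 | 2.40 | 1.304 | 23.3% | 13.3% |

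A beta-binomial simulation with 86 men per arm and a 40% testing rate agreed with the formula (8.1% and 11.2% for groups of 11 at ICC 0.05 and 0.10; 13.4% in the last row). At ρ = 0 there is no error.

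**HCF clustering in the same test, for comparison.** With 21.5 men per HCF in both arms and ICC 0.10, DE = 3.05 and type I error = 2·(1 − Φ(1.96/√3.05)) ≈ 26%. This is about twice the worst retreat case above.

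**Effect on a mixed model with an HCF intercept only.** Simulated with 4 HCFs per arm, 27 men per HCF, no arm effect, a Wald z test, 600 runs per setting, and ICCs on the logit scale. Entries are model SE / true SD of the log odds ratio.

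| HCF ICC | No retreat effect | Retreat ICC 0.10, about 9 men: nested in HCF / spread over HCFs | Retreat ICC 0.10, about 13 men: nested / spread |
|---|---|---|---|
| 0 | 1.07 | 0.97 / 0.91 | 0.96 / 0.92 |
| 0.05 | 0.93 | 0.92 / 0.87 | 0.87 / 0.85 |
| 0.10 | 0.85 | 0.90 / 0.85 | 0.87 / 0.83 |

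Simulation error is about 3% on each SD, so small differences should not be read. At HCF ICC 0.05, rejection rises from 9.2% to 12.3% with 9 men per retreat spread over HCFs. At HCF ICC 0.10 the SE is already too small because there are only 8 HCFs, and retreats add no clear further loss.

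**The case against.** A reader might infer that the standard error is certainly too small. The article does not support that. The error needs a positive retreat ICC and, for the mixed model, retreats that cut across HCFs. Neither is stated. The nurses' invitations could even align retreats with HCFs, and an HCF intercept would then absorb most of the retreat variance.

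A reader might also infer that intervention men share peer mentors, as a second grouping. The article does not say so: Table 1 describes HIVE³ as one-on-one contact, and no mentor caseload is given.

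The quoted sentence lists factors in the model and is not a closed list of random effects. The abstract does name a peer-group level, and an unseen analysis plan could settle the structure. This narrows the point but does not remove it. The article itself fixes an uncorrected chi-square as the primary test and names the HCF as the only source of clustering, and a peer-group predictor would not supply the missing variance term.

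It could be argued that the 10% ICC already covers group clustering, since 86 per arm fits clusters of about 12. The cluster unit is not stated, and an allowance in the sample size would not correct the standard error in the analysis.

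Finally, a retreat term added only to the additional model would leave the primary p-value unchanged, and with about 6 to 11 retreats (86/15 to 86/8) its variance would be poorly estimated. Both points stand and shape the fix.

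**Conclusion.** The point holds in conditional form. The design is partially nested, the primary test ignores this, and the abstract and the Statistical analysis plan section disagree on a peer-group level. If testing is correlated within retreats, the chi-square's standard error is about 3 to 23% too small and its type I error about 6 to 13% from this source alone. Those ranges rest on an assumed 8 to 15 analysed men per retreat and an assumed ICC of 0.02 to 0.10.

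For the HCF-only mixed model the loss is smaller, depends on how retreats map to HCFs, and is not clearly visible at an HCF ICC of 0.10, the value of the one ICC the article states. It would be wrong to read the missing retreat term as the main defect: neglect of HCF clustering in the chi-square is larger. The point still deserves action, because the trial is meant to supply an effect size and retreat membership has to be recorded while the trial runs.

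**What to change.** 1. Reconcile the abstract with the Statistical analysis plan section on the peer-group level, and state the retreat size and how retreats map to HCFs.
2. Record each intervention man's retreat ID, both assigned and attended.
3. Base the arm test and the effect-size interval on a logistic mixed model with an HCF effect and a retreat random intercept in the intervention arm only, treating each control man as his own group. Use a small-sample reference distribution, such as t on 8 − 2 = 6 degrees of freedom, in place of z. The unadjusted chi-square can stay as a descriptive result.
4. Name a fallback in advance for non-convergence or a zero variance estimate, for example a linear mixed model with the same terms, with retreat-robust errors as a sensitivity analysis.
5. Report the retreat ICC with its confidence interval, and say that it will be imprecise.

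The cost is an extra ID field and one model term. The interval will be slightly wider for the retreat term, beyond whatever the HCF correction adds, and boundary estimates are possible with so few retreats and HCFs.
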